## Abstract

**Background:**

There is numerous literature on mechanisms underlying variability of practice advantages. Literature includes both behavioral and neuroimaging studies. Unfortunately, no studies are focusing on practice in constant conditions to the best of our knowledge. Hence it is essential to assess possible differences in mechanisms of neuroplasticity between constant vs. variable practice conditions. The primary objectives of the study described in this protocol will be: (1) to determine the brain’s structural and functional changes following constant and variable practice conditions in motor learning (structural and functional magnetic resonance imaging, MRI); (2) to determine the EEG activation and connectivity between cognitive, sensory, and motor cerebral cortex areas (central, temporal, parietal, occipital) in constant and variable practice conditions and as a function of practice time.

**Methods:**

The study will follow the interventional (experimental) design with two arms (parallel groups). Fifty participants will be randomly assigned to two groups practicing in constant (CG) and variable conditions (VG). CG will be practicing only one pattern of step isometric contractions during unimanual index finger abduction, i.e., 90 trials in all training sessions, whereas VG will practice three different patterns. Each will be practiced 30 times per session in variable conditions. Resting-state fMRI, EEG (cortical networking), and motor task proficiency will be examined before (pre-) and after practice (post- and retentions tests).

**Discussion:**

Findings will enhance our understanding of structural and functional neural changes following practice in constant and variable conditions. Therefore, the study can be considered pure (basic) research (clinical research in healthy individuals).

**Clinical Trial Registration:**

Study registered at clinicaltrials.gov (ID# NCT04921072) on 9 June 2021. Last version update: 21 December 2021.

The protocol has been prepared according to the complete SPIRIT checklist (http://www.spirit-statement.org/), although the item order has been modified in order to comply with the manuscript structure.

## Introduction

### Background and Rationale

The problem of efficiency in motor learning under variable and constant practice conditions has been addressed in many research for many years, e.g., it has a special place in Schmidt’s schema theory (Schmidt, 1975, 2003). The theory assumes that practicing many variations of skill develops memory representation (motor schema) better. As a result, a better-developed schema positively affects the transfer of a skill performed in a novel situation.

We also know that variable practice involving the practice of several variations of a skill benefits learning differently than practice in constant conditions, i.e., a practice that involves only one variation of a skill (Czyż, 2021; Kim et al., 2021b). The variable practice results in better retention and transfer (Schmidt and Lee, 2011). The performance of a skill practiced in variable conditions is more accurate and stable (Keetch et al., 2005; Breslin et al., 2012). In contrast, practicing only one variation of a skill better refines recall schema (Keetch et al., 2005; Breslin et al., 2012). It means that the motor program (which serves as an, “example,” while executing a movement) is developed better (Keetch et al., 2005). The trained variation of a skill (in constant practice) produces an advantage in performance as compared to the same variation of the skill that was practiced in variable conditions (assuming that variable and constant practice had similar capacity; Schmidt and Lee, 2011). This finding has an important implication for those who want to master their skills. If one wants to be good at performing only one variation of skill, one should practice in constant conditions. In contrast, if one wants to be good in more than one variation of skill and generalize the experience to novel situations, an individual should practice in variable conditions (Czyż and Moss, 2016). As one can see, this implication is practical, although the mechanisms underlying this distinction and differences are unknown.

It is unquestioned today that learning new motor skills dynamically changes the brain structure and function, i.e., the brain is neuroplastic (Mang et al., 2020). The neuroplasticity of the brain is specifically conspicuous in the progression of motor learning. As it was reported in previous research, cortico-striatal and cortico-cerebellar systems play an essential role in motor skill acquisition (Doyon et al., 2009; Lohse et al., 2014). However, both of these systems differ in terms of their role as the learning progresses. Cortico-striatal system (associative/premotor brain regions) is primarily engaged in the initial phase of learning, i.e., in cognitive functioning and sensory processing. The cortico-striatal system consists of the dorsolateral prefrontal cortex, rostral premotor areas, inferior parietal cortex, cerebellar cortex, and rostral basal ganglia (Lohse et al., 2014).

On the other hand, the primary motor cortex, supplementary motor area, dentate nucleus of the cerebellum, and putamen, are becoming more active in the later phase of motor learning. These brain regions constitute cortico-cerebellar system (sensorimotor network; Mang et al., 2020). It has been hitherto evinced that the brain structure changes due to motor learning. There was an increase in gray and white matter mass after a new motor skill (bimanual three-ball juggling) was practiced (Draganski et al., 2004, 2014; Boyke et al., 2008). Structural changes are noticeable in MRI, although none of the previous research focused exclusively on practice conditions. Moreover, none of the previous research focused on what role these systems play in learning under different conditions and how the different roles the systems may play affect the structural neuroplasticity, including gray and white matter. Therefore, we decided to use MRI to assess whether and what changes in brain structures follow skill practicing in constant and variable conditions.

Apart from potential structural differences, functional neuroplasticity will also be assessed. A lesser degree of cognitive involvement during movement execution may be associated with lower activation in the sensorimotor cortex (Cheng et al., 2015). On the other hand, increased cognitive involvement may be expected in variable conditions due to, e.g., due to stimulus identification or decision making. Therefore, an assumption that decreased cognitive involvement and, as a result, decreased prefrontal cortex activation in constant practice conditions sounds reasonable. Moreover, we may hypothesize that practicing and learning in constant conditions will be characterized by lower sensorimotor cortex activation since there will be decreased control during the motor performance, which leads to more adaptive motor performance. Vernon and colleagues (Vernon et al., 2003) showed that in order to reduce the somatosensory interference in information processing, their participants enhanced SMR power as indexed by increased SMR/theta and SMR/beta ratios. As a result, participants were able to maintain perception and, to a lesser extent, focused attention. Assuming that parametrization has to take place under variable practice conditions every time one changes performance from one variation of skill to another, demand on cognitive resources (perception and attention) would be bigger than in constant conditions, in which parametrization is facilitated. Consequently, the variable practice group should increase SMR as compared to the constant practice conditions group.

There have been no previous studies on cortical networking in constant and variable practice and motor learning; we decided to assess such communication measuring EEG coherence (Deeny et al., 2009). A significant linear relationship exists between time series simultaneously recorded from two locations (high coherence), indicating communication between these areas of the cerebral cortex. In contrast, low coherence indicates the opposite (Deeny et al., 2009). We may expect decreased coherence between premotor (Fz) and motor (C3, C4) areas of the cortex and between the premotor and occipital regions as the practice of a visuo-motor task progresses (Busk and Galbraith, 1975). However, if the constant and variable practice condition groups receive the same amount of practice, we may expect that pairing electrodes in specific regions will be undifferentiated (Deeny et al., 2003). Lelis-Torres and colleagues (Lelis-Torres et al., 2017) noted that when investigating the cognitive effort involved in random compared to constant practice schedules, the random practice induced significantly greater cognitive effort than constant practice. Throughout the practice, both task engagement and mental workload decreased more in the constant practice condition than in the random practice condition. However, the random schedule is only one variant of variable practice. Another extreme is the blocked practice schedule. Variable practice in blocked order assumes that a learner is practicing many skill variations but in blocks (or time). Although, authors agree that this is also variable practice (Van Rossum, 1987; Czyż, 2021), some doubt whether this variability differs from constant practice (Kim et al., 2021b). This ambiguity will be tested in our study.

### Objectives

The primary objectives of our study are:

1. To determine functional brain changes following (neural underpinnings of) constant and variable practice conditions in motor learning (resting-state fMRI).

2. To determine the EEG activation and connectivity between cognitive, sensory, and motor cerebral cortex areas (central, temporal, parietal, occipital) in constant and variable practice conditions and as a function of practice time.

### Trial Design

The study will follow the interventional (experimental) design with two arms (parallel groups). The study protocol was approved by Masaryk University Research Ethics Committee (EKV-2021-057) and was registered at clinicaltrials.gov (ID# NCT04921072). The outline of the study design is shown in Figure 1.

**Figure 1 F1:**
[figure not shown]
Flowchart of the study.

## Methods

### Participants, Interventions, and Outcomes

#### Study Setting

The study will be conducted at Multimodal and Functional Imaging Laboratory (MAFIL), Masaryk University, Brno, Czechia, and at CEITEC and Faculty of Sport Studies, Masaryk University, Brno, Czechia.

### Eligibility Criteria

#### Inclusion Criteria

Young, healthy male and female adults (20 years old–35 years old) will be recruited. Inclusion criteria: no history of epilepsy, any known neurological disorder, no psychiatric history, were medication-free during the previous 14 days prior to participation, had not used alcohol within the previous 24 h and were not pregnant (Kim et al., 2021a). Participants will be excluded if they were a musician or a professional typist, or had any contraindications to MRI, significant medical conditions that prevent them from performing the task (Lin et al., 2018), or scored less than three on the Mini-Cog^TM^ test (Borson et al., 2003).

Participants’ handedness will be determined using the German version of the Edinburgh Handedness Inventory (EHI) questionnaire (Oldfield, 1971; Loffing et al., 2014).

#### Exclusion Criteria

Participants who do not meet the inclusion criteria will be excluded. Additional exclusion criteria for the MRI experiments will be claustrophobia, pacemaker, and ferromagnetic metal material in the body. Participants declaring any contraindications for physical activity or being unhealthy will be excluded from the study.

#### Recruitment

A total of 50 participants will be recruited. We will address potential participants (whatever contact is preferable) from the already existing databases at CEITEC with people willing to be contacted and willing to participate in the neuroimaging projects. We will also utilize participants invited by doctoral students involved in the project. These will identify further potential participants.

### Interventions

#### Explanation for the Choice of Comparators

The constant practice condition group will be used as a comparator. Although, one could choose the variable practice conditions (in blocked form) group, as well. They, i.e., constant and variable practice conditions, are but two extremes of one continuum (Czyż, 2021). Therefore, our choice is arbitrary (comparator could be either extreme).

#### Intervention Description

##### Motor Task

The participants will be performing unimanual (with dominant right hand) index finger abduction (UIFA) using custom-made equipment (Figure 2) consisting of:

**Figure 2 F2:**
[figure not shown]
Set-up for the unimanual index finger (UIFA) abduction motor task.

***(a)**
wooden table/board* to support forearm during testing;

***(b)**
force transducer* to measure isometric force during UIFA motor task; the force transducer (WMC, Interface, Arizona, USA) used in our device is highly sensitive to levels of generated isometric force during the UIFA motor task (force measurement range 0–120 N); the output force signal of the transducer will be filtered and amplified with *SGA conditioner* (Interface, Arizona, USA), and then directed to a *multichannel CED card* (Cambridge Electronic Design, Ltd., Cambridge, UK) and recorded using *Spike* 2 s*oftware, version 7.10* (Cambridge Electronic Design, Ltd., Cambridge, UK). The sampling frequency of simultaneously recorded force signals will be 2,048 Hz;

***(c)**
wooden button connected to the force transducer* to transfer a force generated by index finger to force transducer; the wooden button is shaped to arched shape of the region of middle phalanx of index finger; and *small mounting metal and plastic elements* (laminas, nuts, and screws) used to connect elements to each other and to attach elements to the wooden table/board;

***(d)**
two supporting Velcro straps* to stabilize fingers that are not engaged in UIFA motor task; the first strap will stabilize the thumb finger, and the second strap will stabilize the third to fifth fingers (in the tested hand); this way, we will isolate the abduction movement of the index finger (UIFA);

First, the participants will be asked to perform three 5 s ongoing trials of maximal voluntary isometric contractions (MVIC) during the UIFA (MVIC-UIFA), separated by 3 min rest intervals. The MVIC-UIFA force value will be then obtained as an average value calculated from the three MVIC-UIFA trials.

Based on the MVIC-UIFA force value, an automatic algorithm of UIFA force feedback system (implemented in the CED Spike2 environment) will be able to set automatically the percentage submaximal level of force to be achieved by tested participants while performing various specific patterns of step isometric contractions (SPSIC) during UIFA. Each SPSIC will be a sequence of five consecutive different percentage UIFA force steps (the range of percentage steps: 10%, 20%, 30%, 40%, 50%, 60%, 70%, 80%, and 90% of MVIC-UIFA force) to be achieved by the participants (as presented with black schemes on Figure 3).

**Figure 3 F3:**
[figure not shown]
Exemplary scheme of the motor task displayed during tests and training. The final values of UIFA task during each SPSIC are not shown as we would like to ensure the novelty of the task to the participants.

Each of the five steps of a single SPSIC will be reached as fast as possible and sustained for 2 s, which gives a 10 s performance time for each SPSIC. Participants will perform SPSIC with 10 s rest intervals between each SPSIC (as in Figure 3).

CG and VG will differ in terms of practiced schemes. CG will be practicing only one SPSIC scheme: SPSIC 1. It means that 90 trials in all training sessions will consist only of SPSIC 1. On the other hand, VG will practice three SPSIC’s (1–3). Each SPSIC will be practiced 30 times per session in variable conditions, which means that each session will consist of 90 SPSIC like in CG.

Thus, taking together the performance time of 90 SPSIC’s (90 SPSIC’s × 10 s = 900 s) and 90 10 s lasting rest intervals (900 s in total), the whole SPSIC motor task performance will last about 1,800 s ≈30 min. After adding the MVIC-UIFA’s performance time (3.5 min), the whole UIFA motor task performance time during the testing session will be about 35 min. The total number of trials and time of training sessions will be the same in both groups, which is consistent with the previous variability of practice study design (e.g., McCracken and Stelmach, 1977). There will be one training session each working day for 3 weeks, which means each participant will accumulate 15 training sessions in total, 1,350 trials. Given the structural changes in MRI (specifically DW-MRI) may be conspicuous after a 3 week discrimination training based on Braille reading (Debowska et al., 2016), we assumed that 3 weeks of training should be enough to observe any structural changes in both groups.

On the other hand, structural changes in gray matter were observed after several hours of training in jugglers in a study by (Draganski et al., 2004). They performed scans in participants who were able to bimanually juggle with three balls for at least 60 s and noticed structural changes in the fusiform gyrus, the medial frontal gyri, and the inferior parietal lobule. Although they did not provide when participants achieved the targeted juggling time (i.e., 60 s), it may be assumed it did not take long. It usually takes hours or days to juggle with three balls (Beek and Lewbel, 1995). In experiments by Knapp and Dixon (1952), participants with no previous juggling experience were able to make 100 consecutive catches after 65–77 trials on average. On the other hand, 3 week training is considered as a long-term learning (Floyer-Lea and Matthews, 2005). Therefore, we assumed that 3 weeks of training should be sufficient to induce structural changes in the brain after our training program.

### Criteria for Discontinuing or Modifying Allocated Interventions

Participants who will not participate in all training sessions will be excluded from the study. The obtained will be deleted.

### Strategies to Improve Adherence to Interventions

Participants will be contacted on a daily basis in order to confirm their availability and willingness to participate in the study.

### Relevant Concomitant Care Permitted or Prohibited During the Trial

There are no relevant concomitant care or interventions that are permitted or prohibited during the intervention.

### Outcomes

Primary Outcome Measure:

1. Brain structural and functional changes following constant and variable practice conditions in motor learning (structural, diffusion, and resting-state fMRI):

Structural, diffusion, and resting-state functional scans will be acquired both prior to and after the 3 weeks of practicing the unimanual index finger abduction motor task. High-resolution T1-weighted (MPRAGE) and FLAIR images will be exploited to assess gray matter changes. Diffusion-weighted (DWI) data will be used for probabilistic tractography to obtain specific tracts that will be analyzed in terms of alterations in fractional anisotropy, mean, radial, and parallel diffusivity. In addition, whole-brain white matter microstructural changes will be assessed using Tract-Based Spatial Statistics (TBSS).

Regarding resting-state fMRI data, BOLD multi-echo echo-planar imaging fMRI sequence will also be performed. In addition to resting-state functional connectivity (rs-FC) analysis among regions of interest, an Independent Component Analysis will also be used to evaluate rs-FC changes of large-scale brain networks of interest.

2. EEG brain waves characteristics and motor task proficiency outcomes (estimated from simultaneous EEG and force recordings during motor task performance, i.e., UIFA) differences in constant and variable practice conditions in motor learning and as a function of practice time:

To record bioelectrical signals from the brain cortex (EEG) during the performance of unimanual index finger abduction (UIFA) motor tasks, we will use the scalp 256-channel EEG data acquisition system (Electrical Geodesics, Inc., Eugen, OR, USA) with sponge electrodes (the “wet” EEG system by Electrical Geodesics, Inc. Eugen, OR, USA). The force induced during the UIFA will be recorded and visualized for participants (as feedback) using the same custom-made system as described in the Section “Intervention Description”. Also, during the UIFA performance, the same force signal will be sent synchronously to the EEG acquisition system (Electrical Geodesics, Inc., Eugen, OR, USA), and will be recorded simultaneously. The force signals will be used as triggers for subsequent EEG analysis.

Two types of UIFA motor paradigms will be used during simultaneous EEG and force recordings in pre- post-, and retention tests, i.e., (1) the UIFA SPSIC paradigm (SPSIC—step isometric contractions) and (2) UIFA MRCP paradigm (MRCP—motor-related cortical potential).

The participants from VG will perform three types of SPSICs (1–3), each repeated 15 times (together 45 trials), but the participants from CG will perform 45 times of one type of SPSIC. This SPSICs will be analyzed in the frequency domain using force signal as a trigger for extracting SPSIC sequences related to time frames of EEG time series data. We will estimate EEG signal’s power spectrum density (PSD) for sensorimotor rhythm (SMR, frequency band 12–15 Hz) as well as for other frequency bands: delta (0.5–4 Hz), theta (4–8 Hz), alpha (8–14 Hz), beta (14–35 Hz) and gamma (35–70 Hz). PSD-EEG analysis will reveal the level of the electrical activity of cortical regions engaged during UIFA motor tasks performance under the constant and variable practice conditions. We will also estimate coherence between EEG signals (EEG-EEG coherence) from electrodes in a chosen region of interest based on the PSD-EEG analysis. Analysis of EEG-EEG coherence calculates the linear relationship between the power spectra of two EEG signals taken from two EEG electrodes placed on the scalp. A significant linear relationship existing between time series simultaneously recorded from two locations (high coherence) indicates a high level of functional communication (connectivity) between these areas of the cerebral cortex, whereas low coherence indicates the opposite.

Both groups will perform 40 MRCP trials, i.e., 10 s radial abduction to 20% MVC of UIFA task and 10 s rest. The MRCP will provide a reliable time-domain estimation of the amplitude, latency, source, and connectivity analysis. The EEG signals recorded during the MRCP paradigm will be analyzed using: (1) averaging technique to assess an amplitude of MRCP showing the level electrical activity of cortical regions engaged during motor task performance, (2) EEG source analysis, showing current dipole of activation as a model of the electrical current, that characterizes of location, orientation and strength or amplitude [expressed in dipole moment (nAm)], which describes the directional activity of brain region engaged in a motor task, and (3) time-frequency and connectivity analysis, to explore the strength of functional coupling between cortical regions responsible in motor preparation and execution. We will analyze the EEG data in co-registration with individual T1 structural MRI scans in the Talairach space, a 3-dimensional human brain coordinate system used to map the location of brain structures independent from individual differences in the size and overall shape of the brain.

UIFA motor task proficiency outcomes for the UIFA SPSIC and UIFA MRCP will be obtained based on the force signal processing and analyses in the time domain. We will estimate a motor performance accuracy based on the error percentage of achieved force level in reference to the given target force level while performing the various sequences of SPSIC-UIFA motor tasks. Also, we will assess the speed of force generation by estimating the time and rate of force development during the execution of the various sequences of SPSIC-UIFA motor tasks.

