### Statistical Methods

#### Statistical Methods for Primary and Secondary Outcomes

In order to compare groups practicing in constant and variable practice conditions in terms of brain’s structural and functional changes, repeated measures ANOVA with time as a within-participants factor, and practice condition as a between participants factor, with *post-hoc* tests will be used. The relationship between MRI brain changes and motor task proficiency will be evaluated using partial correlations.

Frequency analysis will be performed separately for each EEG channel and trial using fast Fourier transform (FFT). Significant differences against baseline will then be compared between participant groups. Connectivity analysis will be performed using the calculation of coherence (Nunez et al., 1997, 1999) between channels of interest. Results will be statistically compared between participant groups. Because of the multiple usages of statistical tests, multiple comparison corrections will be used.

Motor task proficiency will be assessed using parametrical or non-parametrical tests, depending on the results of the assumption tests (homogeneity, normality). The possible tests include but are not limited to correlations, t-test, and analysis of variance (2 × 3 model; two practice conditions × three time points) with the following *post-hoc* analysis for all significant main effects.

We may use Bayesian equivalents of the tests mentioned above.

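### Primary outcome 2 defines EEG coherence in conflicting terms and reads high scalp coherence as communication, although zero-lag spread and source power alone can raise it

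*Protocol article*

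**What the plan says.** Objectives makes EEG activation and connectivity, by practice condition and over practice time, the second primary objective. For the step-contraction (SPSIC) task, Outcomes says that coherence will be estimated between electrodes in a region chosen from the power analysis. It then explains the measure: "Analysis of EEG-EEG coherence calculates the linear relationship between the power spectra of two EEG signals", with both signals coming from scalp electrodes.

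The next sentence describes it differently: "A significant linear relationship existing between time series simultaneously recorded from two locations (high coherence) indicates a high level of functional communication". Background and Rationale agrees with this second description: "A significant linear relationship exists between time series simultaneously recorded from two locations (high coherence), indicating communication between these areas of the cerebral cortex".

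Outcomes also fixes how the value is to be read. A high value "indicates a high level of functional communication (connectivity) between these areas of the cerebral cortex, whereas low coherence indicates the opposite".

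Statistical Methods for Primary and Secondary Outcomes names coherence between channels of interest, cites methods papers and gives no formula. The sentence on spectral analysis reads: "Frequency analysis will be performed separately for each EEG channel and trial using fast Fourier transform (FFT)".

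In the paragraph on the movement-related potential (MRCP) task, Outcomes adds: "We will analyze the EEG data in co-registration with individual T1 structural MRI scans in the Talairach space".

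**The concern.** There are two separate problems.

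**Definition.** The only sentence that says what is calculated refers to two power spectra. A power spectrum keeps the squared amplitude at each frequency and discards phase. A relation between two power spectra therefore reflects similar spectral shape or shared amplitude change, not coupling of the signals. The adjacent sentence and the rationale describe something else.

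**Reading rule.** Even correctly computed coherence between two scalp electrodes is not specific to communication. One source that reaches both electrodes at zero lag produces coherence by itself, and the amount depends on how strong that source is relative to the rest of the signal. Background and Rationale predicts higher SMR power in the variable group than in the constant group, and Outcomes lets the power analysis choose the coherence region. A power effect could thus appear a second time as a connectivity effect, and the two halves of primary objective 2 would no longer be distinct findings.

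**Working it through.** The plan states no figure for this point, so there is none to reproduce.

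**Inputs from the protocol article.** 45 SPSIC trials per test: 45 of one pattern in the constant group, 15 of each of three patterns in the variable group (Outcomes). 10 s per trial (Intervention Description). SMR band 12–15 Hz (Outcomes).

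**Assumptions.** The spectral shapes, the 256 Hz sampling rate and 1 s segments of the simulation, and the leakage fractions and source powers below are not in the article.

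**Step 1: the two descriptions.** Let X and Y be the complex Fourier coefficients of the two channels. Averaging over segments or trials, Sxx is the mean of |X|², Syy the mean of |Y|², and Sxy the mean of X times the complex conjugate of Y. The measure of linear relationship between the time series at a given frequency is

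coherence = |Sxy|² / (Sxx · Syy).

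The power spectra are Sxx and Syy. Sxy cannot be recovered from them, so the sentence on power spectra and the sentence on time series describe different quantities.

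**Step 2: how far apart they can be.** Simulation of 45 trials of 10 s, 20 replicates:

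- Independent channels with 1/f-type spectra: the correlation of the power spectra over 1–70 Hz is 0.999–1.000, and within 12–15 Hz it is 0.24–0.93. Coherence is 0.001–0.002.
- Independent channels with flat spectra: the power-spectrum correlation over 1–70 Hz is 0.20.
- Independent channels, 12–15 Hz power correlated across trials: −0.06 to 0.05.
- Fully coupled channels with differently shaped spectra: the power-spectrum correlation is −0.43. Coherence is 0.98.

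The literal sentence can mislead in either direction, and how it does so depends on which correlation is meant.

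**Step 3: zero-lag spread with correct coherence.** Take independent sources s1 and s2 of equal power (set to 1), with x = s1 + a·s2 and y = s2 + a·s1. Then Sxy = 2a and Sxx = Syy = 1 + a², so

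coherence = (2a)² / (1 + a²)².

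- a = 0.2: 0.16 / 1.0816 = 0.148
- a = 0.3: 0.36 / 1.1881 = 0.303
- a = 0.4: 0.64 / 1.3456 = 0.476

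Simulation at a = 0.3 gave 0.30. The sources do not communicate. Sxy is real, so the imaginary part of coherency is 0.

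**Step 4: dependence on source power.** Let one source of power p reach both electrodes equally, with independent activity of power 1 at each. Then Sxy = p and Sxx = Syy = 1 + p, so

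coherence = (p / (1 + p))².

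- p = 1: (1/2)² = 0.25
- p = 2: (2/3)² = 0.44

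Doubling the source power raises coherence by 0.19 with no change in coupling. What counts is relative power: if shared and independent activity are scaled together, the value does not move.

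**Step 5: number of averages.** With no coupling, estimated coherence averages about 1/K for K independent averages: 1/45 = 0.02 and 1/15 = 0.07. If coherence were formed per pattern in the variable group and over all 45 trials in the constant group, the floor alone would differ by about 0.04.

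**The case against.** The strongest reply is that the sentence on power spectra is a loose explanation and not the computing rule. Coherence is a named quantity with a standard definition. Outcomes and Statistical Methods both name it, the latter citing methods papers, and the neighbouring sentence and the rationale describe it properly. Ordinary software would compute ordinary coherence. This stands. A reader might infer that the wrong measure will be used and will always be high for unconnected areas. The article does not support that: its other statements point to ordinary coherence, and Step 2 shows that even the literal reading gives values near 0 or 0.2 in some cases.

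A reader might also infer from the FFT per channel and trial that coherence will be formed within a single trial, where it equals 1. The article does not say so. A per-trial FFT is the usual first step before averaging, and connectivity has its own sentence.

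On leakage, the reply is that fixed spread is common to both randomised arms, so it raises the level without biasing the comparison, and that the choice of a robust estimator belongs in an analysis plan that is not shown. The first part holds only while relative source power is equal across groups and times (Step 4), and the article itself predicts a group difference in SMR power. The second part is fair for the choice of estimator. It does not cover the reading rule, which the article states outright.

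Finally, the sentence on T1 co-registration is not expressly limited to the MRCP data, so source-level work on the SPSIC data may already be intended. The article nevertheless describes SPSIC coherence as taken between scalp electrodes.

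**Conclusion.** Both parts hold, with different weight.

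The definition in Outcomes is technically wrong and contradicts the sentence after it and Background and Rationale. It needs reconciling. It does not show that a wrong analysis will be run.

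The reading rule is the more substantial part. Ordinary scalp coherence of about 0.15 to 0.48 can arise with no communication, assuming 20% to 40% zero-lag leakage between two equally strong independent sources. It can move from 0.25 to 0.44 when one shared source doubles in power against constant local activity. These figures illustrate size under assumed inputs and are not estimates for this trial. They suffice to show that a difference in coherence between groups or over time cannot by itself be reported as a difference in communication, least of all where SMR power is expected to differ.

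**What to change.** 1. In Outcomes, replace the sentence on power spectra with a definition: coherence is |Sxy|² / (Sxx · Syy) per frequency band, with cross- and auto-spectra averaged before the ratio is formed, over the same number of segments or trials in every participant and test. Bring Background and Rationale and Statistical Methods into line with it.
2. Report beside it, on the same SPSIC data, the imaginary part of coherency, or source-level coherence using the T1 co-registration already planned.
3. Replace the reading rule: interpret a coherence difference as communication only when the measure in item 2 supports it.

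The cost is a few sentences and some additional computing on EEG and T1 data that will be collected anyway. The drawback is that the imaginary part also discards true zero-lag coupling, so it supplements ordinary coherence and does not replace it.
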